**Fig. 1 Fig1:**
[figure not shown]
Participant timeline

The sample size target of 140 (70 in the intervention group, 70 in the waitlist control group) was based on an a priori power analysis to achieve 80% power to detect a moderate effect size (*d*= 0.50) between the groups at 10 weeks on our primary outcomes. Our sample size requirement assumes a conservative 20% attrition at each time point (original COMPASS study saw 15% attrition at 12 months) [27]. We also assumed an AR(1) correlation structure with rho = 0.7 for repeated observations within each worker. The power calculation also takes into account a conservative intracluster correlation coefficient within each virtual group of 0.10 (in the original COMPASS trial, ICC range was 0.001–0.086) [27]. The estimated effect size of *d* = 0.50 is the average effect size for safety changes at 6 months in the original COMPASS trial, which represents a reasonable estimated effect for COMPASS-NP for pain-related limitations outcomes.

### Inclusion/exclusion criteria

The inclusion criteria will consist of adult HCWs reporting chronic pain (pain lasting 3 + months and > 4 average intensity), the current presence of pain interference with work (response of “agree” or “strongly agree” on single-item), currently working ≥ 4 h per week, and access to the Internet with a video-capable device (e.g., smartphone, tablet, or computer). The exclusion criteria will include prior exposure to the original COMPASS program, childbirth in the prior 6 months or current pregnancy, major surgery in the prior 6 months or scheduled major surgery during the study period, and any significant psychiatric problems resulting in hospitalization during the prior 6 months.

Study partner organizations will send HCW recruitment emails and also advertise the opportunity through websites, newsletters, and other established communication channels (e.g., social media). Interested HCWs will complete an online eligibility screener survey along with their schedule availability and technology comfort level. Qualifying HCWs will be contacted by the study staff by phone to discuss the study and complete an informed consent process. Once 2 groups of 10 HCWs in the same state are created, those groups will be randomized. The group receiving the intervention first will be mailed program materials and then contacted by their facilitator to schedule a pre-program call for coaching on web-based technology for group meetings.

COMPASS-NP group facilitators will be recruited from existing professional trainers or staff from partner organizations and complete training prior to leading groups (see the “ Intervention condition” section).

### Participant compensation

Facilitators and workers will be paid an hourly wage for facilitating/attending COMPASS-NP meetings (approximately $15/h for workers, $35/h for facilitators), which is consistent with our partner organization’s training practices and promotes retention. HCWs who complete the online ergonomic tool self-assessment will be provided the tools they select directly, or through a voucher, up to a value of approximately $100. HCWs will receive escalating incentives for completing surveys ($20 at baseline, $40 at 10 weeks, $60 at 20 weeks).

### Intervention condition

COMPASS-NP facilitators will complete an adapted version of an established online COMPASS Facilitator Orientation. This facilitator training describes the purpose of each meeting step followed by a video of a COMPASS facilitator and group role-playing that step. A facilitator handbook will be created to guide pre-program technical coaching of HCWs, as well as running COMPASS-NP meetings using Microsoft Teams or comparable technology. The study staff will further support facilitator onboarding by observing their initial group meetings and completing debriefing and coaching conversations afterward.

COMPASS-NP will involve 10, weekly virtual meetings (1.5 h each). Virtual meetings will be held with the Microsoft Teams video conference software or a comparable platform. HCWs will be mailed scripted guidebooks, a pain journal to track their pain and pain management behaviors, and instructions for joining virtual meetings. Facilitators will provide one-on-one technical coaching with the video conference platform with each participant prior to the first meeting, and then lead groups during that first meeting to model the leader role in the process. In subsequent meetings, facilitators will step back to monitor and support workers as they take turns serving as peer leaders. The scripted guidebook approach requires minimal training for peer leaders and group members to effectively participate. The primary mode for workers to learn the peer leader role is the scripted content for meeting one (see overview of topics below) and watching the facilitator model that role.

The intervention materials for COMPASS-NP will include scripted guidebooks for 10 weekly meetings, as well as the complementary content of an online ergonomic assessment tool, online facilitator orientation training and resources, and a central program website that participants can access for resource materials. The core process and meeting steps from the original COMPASS program will be retained with adjustments such as shortened duration (90 min) and tailoring meetings for workers with chronic pain (Fig. 2).

**Fig. 2 Fig2:**
[figure not shown]
COMPASS for navigating pain meeting steps

These steps include a WorkLife check-in, an educational lesson, group and individual goal setting, a healthy break, a structured WorkLife Support process, and a meeting reflection/summary. Six existing scripted meetings addressing how COMPASS groups work (meeting 1), ergonomics (meetings 4 and 5), communication skills (meeting 7), functional fitness (meeting 8), and stress management/well-being (meeting nine) will be adapted for HCWs with chronic pain. Four new scripted lessons (Fig. 3) consisting of meetings 2, 3, 6, and 10 will address pain education and CBT for pain self-management, based on evidence-based content adapted from *The Pain Survival Guide *[50]*.*

**Fig. 3 Fig3:**
[figure not shown]
COMPASS for navigating pain meeting topics

The online ergonomic assessment tool will be adapted from the NIOSH handbook for HCWs titled *Caring for Yourself While Caring for Others* [53]. This tool will be used as a module homework assignment with follow-up and discussion in the subsequent meeting. Workers will use the tool to select their frequent work tasks from a checklist (e.g., housecleaning, client bathing, client mobility) and then be guided through educational screens based on task selections. These screens will identify the potential hazards associated with each task and methods to control them including low-tech ergonomic tools. HCWs will also receive a report, plus a list of relevant ergonomic tools to select from, and receive (up to $100 in value) based on their common work tasks (e.g., transfer clients from chair to wheelchair slide board and transfer belt).

### Intervention process and data collection

#### General process

Participants will complete online surveys that contain primary and secondary study outcomes at each study time point via REDCap [54, 55]. The post-intervention survey (10 weeks for the initial intervention group, 20 weeks for the waitlist control group) will also include ratings of the overall acceptability of intervention materials, goals, procedures, and target outcomes [56], as well as qualitative questions about the most and least helpful aspects and opportunities for improvement. Facilitators will track attendance and participation levels for each meeting, and this will be affirmed by study staff who 20% of group meetings. The research staff will also conduct interviews with partner organizations, facilitators, and a sample of HCWs to further assess the factors related to the implementation and future dissemination of the program (see the “Qualitative data” section). Participants will be emailed or texted reminders for completing surveys and attending intervention meetings. To further monitor study and intervention participation, researchers will monitor and update met or missed deadlines for study activities and then provide appropriate reminders or support.

Two of our partner organizations, the SEIU 775 Benefits Group and the Oregon Home Care Commission (OHCC), already offer well-attended live group online trainings. Attendance and a basic affirmation of participation level (e.g., did each participant take a turn reading the script) will be tracked by and collected from facilitators. We will also monitor web analytics to measure engagement with online COMPASS-NP materials (e.g., online ergonomic assessment, facilitator training videos, downloadable resources) throughout the intervention. Brief reaction measures will be collected for each meeting via REDCap using an adaptation of the OHCC training evaluation, which includes reaction ratings (affective and utility) for the lesson content, facilitator/trainer performance, and intentions to make changes to benefit the worker and their clients. Global ratings of the social validity/acceptability [57, 58] of goals, processes, and outcomes of the intervention will be collected via REDCap surveys after each group completes the intervention.

#### Quantitative data

Demographic and background survey items will include age, gender, family composition, work tenure, current work hours/clients, additional jobs (paid and unpaid/voluntary), health/injury history, current health conditions and medications, primary language, single- versus multi-income household, total income, and financial strain [59]. We will also measure several psychosocial factors known to be associated with pain and pain management, including stress [60], pain management self-efficacy [61], depressive symptoms [62], anxiety, and sleep quality [63]. We will describe the sample in total and across the participating states.

Pain interference is our primary outcome that will be measured in two domains, work and life. Pain interference is a recommended outcome in pain intervention research [64], and measuring interference with both work and life domains is consistent with integrated TWH approaches to occupational health interventions. Pain interference with work will be measured with the Work Limitations Questionnaire [65], which addresses limitations in four domains of work demands (time, physical, mental-interpersonal, and outputs). Pain interference with life will be measured with the interference subscale from the Brief Pain Inventory (BPI) [66] that addresses pain interference with general activity, walking, work, relations with other people, sleep, and enjoyment of life. The BPI is a validated 32-item measure (*α* = 0.80–0.96) [67] designed to capture a variety of factors, including pain interference, as well as the location, experience, progression, and treatment of pain [68]. It is widely used in pain outcome research [69].

Secondary outcome measures will include pain/injury prevention behaviors, injuries, pain severity, well-being, physical activity, sleep duration and efficiency, change in pain medication use, and risk of opioid misuse. Pain/injury prevention behaviors will be measured using items created in the original COMPASS research [27] that assess ergonomic tool use during housekeeping and client moving tasks and hazard correction in client homes. Injuries (first aid only and lost work time) will be reported for the past 10 weeks. Pain severity (average severity during the past week, 0 = no pain, 10 = worst pain possible) for each body region will be measured with the BPI pain severity subscale [66]. Well-being will be measured with the PROMIS Global-10 items to assess physical, mental, and social health, as well as emotional distress and overall quality of life [70]. Sleep and physical activity outcomes will be gathered using 1-week accelerometer samples at each time point (see methods below). Change in pain medication use (prescription and over-the-counter) will be assessed using a subscale from the BPI that assesses pain medication type, frequency of use (within 24 h), dependence, and concerns. The risk of opioid misuse will be measured with the Screen And Opioid Assessment For Patients With Pain—Revised (SOAPP-R) [71] for workers not currently using opioids and with the Current Opioid Misuse Measure (COMM) [72] for workers currently using opioid medications (each validated for predicting misuse).

Actigraphs (GT3x + BT, Actigraph, Pensacola, FL) will be used to obtain objective measures of physical activity and sleep. Actigraphs will be mailed to participants at each time point to collect 1-week samples of daily physical activity (waist-worn) and sleep duration/efficiency (wrist-worn). Participants will be provided with pre-paid postage envelopes to return devices to researchers. Data processing for actigraphic samples will be completed with a study-specific protocol modeled on methods used in our previously published studies [60, 73].

#### Qualitative data

Throughout the study, correspondence between the research group and partners, and between partners and participants (e.g., study advertisement communications), will be collected/documented for consideration in qualitative data analyses. During planning and coordination meetings, materials and information will be requested from organizational partners regarding their training program systems and resources (training courses offered, healthcare benefits, software platforms used for e-learning or video conferences, certification or continuing education programs and requirements, HCWs’ access to ergonomic tools). We will also request and record information from partners regarding workforce demographics, partner-specific occupational safety and health-related challenges, and plans for future resources and training that may align with COMPASS-NP adoption.

The study staff will conduct post-intervention phone interviews with group facilitators (3 to 7 expected) and organizational partner leaders (minimum 3) to gather direct feedback on the feasibility and quality of the training, perceived program sustainability and accessibility, barriers/facilitators to program adoption and participant engagement (e.g., replicating or replacing the tool provision program), challenges encountered and any innovations or strategies used to meet challenges, and additional experiences. In accordance with the occupational safety and health intervention translation model introduced by Schulte and colleagues [74], data collection will also focus on potential adopters/implementers (e.g., facilitators’ and leaders’), motivation/behavior, attitudes, organizational structures that encouraged or discouraged change, and adequacy/usability of systems within our partnering organizations. Facilitators will be invited to participate in one or more phone interviews following each wave of implementation and with organizational leaders after implementation in their state is complete. Interviews with a subsample of HCWs will also be conducted to complement qualitative data gathered from adopters and implementers. These interviews will focus on workers’ perspectives on how best to identify interested workers, advertise or market the program, and maximize ease of participation. Interview participants will be compensated $40 for each interview as permitted (government leaders may not be able to accept payment).

Interview guides and protocols will be structured based on the narrative approach to qualitative data collection [75]. The narrative interview is typically a collaborative process between interviewer and participant where both work together to generate a story—the narrator tells their story while the interviewer fosters narration through keen observation and deep listening [76]. The interviewer must be emotionally attentive and use prompts to facilitate storytelling more than answers.

### Data analysis, storage and fidelity

#### Quantitative data analysis

We will summarize participant demographics using descriptive statistics and data visualizations (e.g., histograms, scatter plots) to evaluate the differences between study arms. Effectiveness analyses will employ an intent-to-treat approach where participants are analyzed and included according to their randomized condition [77], regardless of their degree of intervention participation. This approach also utilizes all available data from participants across all time points. To test our hypothesis that the intervention group will experience reduced pain interference with work and life, we will evaluate the within- and between-group differences in the magnitude of change in the two primary outcome domains, using a difference-in-differences (DID) approach that suits the between-group and within-group design of this study. The DID approach is a general approach that can estimate relative changes in outcomes within-group and between study groups through a group-by-time interaction group. Specifically, we will implement our DID approach using generalized linear mixed models (GLMM) [78], which offer flexible regression modeling to accommodate for different sources of correlations (e.g. serial and intra-group), categorical and continuous covariates, and fixed and time-dependent covariates. These GLMMs offer a wide range of parametric distributions to model the dependent variables, including logistic regression (binary data), beta regression (percent data), Poisson regression (count data), and Gaussian regression (normally distributed data). For example, to assess the changes in pain interference, a Gaussian linear mixed model can analyze pain interference at baseline, week 10, and week 20 as a function of whether a HCW belongs to the intervention condition, time, the interaction of condition and time, and other potential confounders (e.g., psychosocial factors from our background survey). We will operationalize comparisons by computing interaction contrasts on pre/post-intervention differences within and across groups. Intervention group membership will be the between-subjects factor and pre/post-intervention assessment scores on primary outcomes will be the within-subjects factors. The interaction contrast approach will allow us to efficiently compare the 2 study arms at the end of 10 and 20 weeks on each pain interference measure with a focused, one degree of freedom hypothesis test. Additionally, to take advantage of the full longitudinal data set (baseline, 10- and 20-week time points), we will implement an analysis of response profiles to characterize the patterns of change in the mean response over time in the two arms by treating time as a categorical factor. Our approach will include random effects for virtual group clusters to account for the correlation of outcomes within virtual groups. We will also include random effects for HCWs to account for the correlation of observations within a worker over time. Depending on the distribution of the outcomes of interest, standard errors may be difficult to estimate using standard regression variance output. Thus, if we cannot accurately represent standard errors, we plan to implement bootstrapping to obtain reliable standard errors when appropriate. If imbalances in participant characteristics are observed at baseline, we will consider propensity score weighting to improve efficiency [79]. We will explore missing data and apply standard practices to control for the differences between subjects in missing data or to impute scores if non-trivial levels of missing data are observed. Similar analytic methods will be applied to secondary outcomes, with appropriate adjustments based on the characteristics of the data and distributions. We will follow the CONSORT 2010 guidelines when reporting study results [80].

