Our primary outcome, pain interference, is a widely used target in pain intervention research. It is inclusive of pain-related physical limitations but also addresses pain interference with additional work-life domains (e.g., relationships, sleep, enjoyment of life). Thus, our primary hypothesis is that COMPASS-NP will have more reduction in pain interference with work and life in the intervention group relative to the control group. Our secondary outcomes will evaluate injury and pain prevention behaviors (e.g., ergonomic tool use), occurrence of injuries, pain severity, changes in medication use, risk for opioid misuse, worker well-being, and objective measures of physical activity and sleep (i.e., actigraphic). Implementation measures will explore the process differences across partners’ systems and assess the intervention fidelity and acceptability. Our secondary hypotheses assert that these outcomes will change in favorable directions relative to the control group. These measures will include environmental and system characteristics, HCW attendance and participation in group meetings, HCW and facilitator characteristics and qualitative feedback, and HCW ratings of the acceptability of the goals, processes, and outcomes of the intervention.

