### Participants, recruitment, randomization, and statistical power analysis

HCWs (*n* = 140) with the presence of symptoms of chronic pain will be recruited across Oregon, Washington, and Idaho to participate in this study with the help of our partner organizations: the Oregon Home Care Commission, the Service Employees International Union (SEIU) 775 Benefits Group in Washington, and the St. Luke’s Health System in Idaho. We will perform 1:1 randomization of block size 2 within each state. The randomized groups will be computer generated by the study statistician and kept in sealed envelopes.

The effectiveness and implementation of COMPASS-NP will be evaluated using a mixed-methods hybrid type II evaluation approach [52]. In this cluster randomized waitlist control design, all HCWs will participate in the trial for 20 weeks, with measures collected by online surveys at baseline, 10 weeks (follow-up 1), and 20 weeks (follow-up 2) (Fig. 1). Fourteen groups of 10 workers each will be created based on residence in the same state and schedule availability for attending group meetings. Half of the recruited groups in each state will be randomly selected to complete the intervention during the first 10 weeks, while the remaining groups serve as wait-list controls (i.e., delayed start) during the same period. After 10 weeks, the wait-list groups will initiate the intervention and finish at week 20. Original intervention participants will experience usual practice during weeks 10 to 20. A randomized waitlist study design was chosen because it creates an intervention vs. control group comparison but also permits every participant to eventually receive the intervention. Given our focus on a vulnerable population in high need of interventions, we deemed this to be the best and most ethical approach for our project.

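### The pain interference hypothesis is tested by the same arm contrast at weeks 10 and 20, but an untreated control exists only up to week 10

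*Protocol article*

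**What the plan says.** All references are to the protocol article.

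- **Hypothesis** (Rationale): "COMPASS-NP will have more reduction in pain interference with work and life in the intervention group relative to the control group".
- **Test** (Quantitative data analysis): the paragraph that sets out how this hypothesis is tested uses interaction contrasts from a mixed model to "efficiently compare the 2 study arms at the end of 10 and 20 weeks on each pain interference measure", each with one degree of freedom. Weeks 10 and 20 are treated alike.
- **Analysis set** (same section): under intention to treat, "participants are analyzed and included according to their randomized condition".
- **Design** (Participants, recruitment, randomization, and statistical power analysis): half of the groups start at once, "while the remaining groups serve as wait-list controls (i.e., delayed start) during the same period". Then, "After 10 weeks, the wait-list groups will initiate the intervention and finish at week 20". For the other arm, "Original intervention participants will experience usual practice during weeks 10 to 20".
- **Survey timing** (General process): the post-intervention survey falls at week 10 for the first arm and at week 20 for the waitlist arm.
- **Power** (paragraph after Fig. 1): "80% power to detect a moderate effect size (*d*= 0.50) between the groups at 10 weeks on our primary outcomes".

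The article does not give the week-20 arm contrast a separate role, such as maintenance or description. It does not recode exposure for the waitlist arm after week 10 either: the example model contains condition, time, their interaction and possible confounders.

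**The concern.** The hypothesis needs a control group. The design supplies one for ten weeks and then, deliberately, removes it. The analysis text nevertheless applies the same arm comparison on the primary measures after the control has gone.

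An analyst who follows the text would produce four tests under one efficacy hypothesis (two measures at two times), and the two at week 20 would have no untreated comparator. A null or reversed week-20 result is what a working programme could be expected to give, yet it could be read as loss of effect or as evidence against the hypothesis. A chance positive could be read as further support.

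**Working it through.** **Inputs from the article.** d = 0.50 at week 10; 70 per arm; 20% attrition at each time point; AR(1) correlation 0.7; ICC 0.10; 14 groups of 10.

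**Assumptions.** Two-sided 5% level (the article states none); normal reference distribution; the same 0.50 SD effect in both arms at the end of their own programme; a share r of that effect still present in the first arm ten weeks later. The article gives no figure for r, so a range is shown.

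**Step 1: the plan's own sample size (week 10).**
- Completers: 70 × 0.8 = 56 per arm, 8 per group.
- Design effect: 1 + (8 - 1) × 0.10 = 1.7.
- Baseline-adjusted variance factor: 1 - 0.7² = 0.51.
- n per arm = 2 × (1.960 + 0.842)² × 0.51 × 1.7 / 0.50² = 54.4, so 55.
- Allowing for attrition: 55 / 0.8 = 68.75, so 69 per arm and 138 in total, against 140 stated.
- Power with 56 completers per arm: 81.1%. With a change-score variance factor of 2 × (1 - 0.7) = 0.60 it is 74.5%.

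The stated sample size is therefore reproduced as a week-10 calculation.

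**Step 2: expected arm contrast from baseline to week 20.** A positive value favours the first arm.

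Expected contrast = 0.50 × r - 0.50 = 0.50 × (r - 1).

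**Step 3: chance that the week-20 test is significant.** The baseline-to-week-20 correlation is 0.7² = 0.49. The variance factor is 2 × (1 - 0.49) = 1.02 for change scores and 1 - 0.49² = 0.760 with baseline adjustment. With 56 completers per arm and design effect 1.7, the standard errors are:
- change score: √(2 × 1.02 × 1.7 / 56) = 0.249;
- baseline-adjusted: √(2 × 0.760 × 1.7 / 56) = 0.215.

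| Share kept, r | Expected contrast (SD) | Significant for first arm | Significant for waitlist arm |
|---|---|---|---|
| 0 | -0.50 | about 0% | 52–64% |
| 0.50 | -0.25 | 0.1–0.2% | 17–21% |
| 0.75 | -0.125 | 0.6–0.7% | 7–8% |
| 1.00 | 0 | 2.5% | 2.5% |
| 1.25 | +0.125 | 7–8% | 0.6–0.7% |
| 1.50 | +0.25 | 17–21% | 0.1–0.2% |

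Ranges run over the two variance forms. If attrition compounds to 36% by week 20, the chances change but the expected contrasts do not.

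**Step 4: the other reading, week 10 to week 20.** The first arm's expected change is 0.50 × (r - 1) and the waitlist arm's is 0.50. The contrast is 0.50 × (r - 1) - 0.50: it is -0.50 at r = 1 and -0.75 at r = 0.50. It favours the arm then in the programme, but its comparator has already been treated, so any fading in that arm is added to the apparent effect. This is not intervention against an untreated control either.

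**The case against.** **Week 10 is evidently the efficacy time point.** The analysis text never calls the week-20 contrast primary or confirmatory. The power statement, the period for which the waitlist groups are controls, and the Abstract's description of weeks 10–20 as follow-up for the first arm all point to week 10. This stands: a reader might infer that the plan declares a primary test at week 20, and it does not. But the sentence that specifies the test covers the primary measures, serves the stated hypothesis and gives both times the same role. The fix brings it into line with the rest of the article.

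**The text may mean each arm's own pre/post change.** The contrasts are described as pre/post-intervention differences, and post-intervention differs by arm. This also stands as a possible reading, so the figures in Step 2 apply only to a baseline-to-week-20 contrast. Step 4 shows that the alternative does not supply an untreated comparator.

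**A reader might conclude that the week-20 test could never favour the first arm, at any sample size.** The documents do not support that. It depends on the benefit holding level or fading. If it keeps growing after week 10, the contrast favours the first arm, as the last two rows of the table show.

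**The week-20 arm difference is still a randomised comparison.** True: it validly compares early with delayed start, and convergence is what the design predicts. It need not be deleted, only kept out of the efficacy test.

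**The harm is conjectural, and ranking contrasts can be left to the analysis plan.** No success rule says how a week-20 result would count, and the planned response-profile analysis would show catch-up. The issue, however, is what the article does state: a hypothesis test at week 20, with the response profiles planned in addition to it.

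**Conclusion.** The point holds as a fault in how the hypothesis test is specified. At week 20 there is no untreated control, so the arm contrast does not test the stated hypothesis on either reading.

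For a baseline-to-week-20 contrast, with 0.50 SD in both arms, the expected value is 0 with full retention, -0.25 SD with half and -0.50 SD with none. With half retained, the chance of a significant result for the waitlist arm is 17–21%, although the programme works in both arms. At week 10 the same inputs give 75–81% power. These figures rest on equal effects in the two arms, a two-sided 5% level and an assumed retained share.

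The fault does not reach the week-10 comparison, the randomisation or the target of 140.

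**What to change.** 1. State that the primary hypothesis is tested only by the baseline-to-week-10 arm-by-time contrast on each pain interference measure, and remove week 20 from the hypothesis-test sentence.
2. Report week 20 as supportive, with confidence intervals:
   - maintenance: week-10-to-20 change in the first arm;
   - replication: week-10-to-20 change in the waitlist arm, described as uncontrolled;
   - if kept, the arm difference at week 20, labelled as early versus delayed start, with no efficacy claim drawn from it.
3. Carry the same wording into the analysis plan.

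The cost is a few sentences. No new data, visits or participants are needed, and the week-10 power statement stays as it is.
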